#### Control group

The control group will receive usual gait training delivered by the usual treating physiotherapist. Usual gait training will not be prescribed, but quantified (e.g., time and distance walked, tasks practiced will be recorded) to be able to describe the intervention accurately. The recordings of usual gait training at the beginning and the end of the study end will be examined to check for contamination from the experimental intervention.

### Measurement

Since the main aim the study is to improve physical activity, the primary outcome will be physical activity measured as steps/day over four days at Weeks 0, 8, 26. Secondary measures collected at Weeks 0, 8 and 26 will include walking ability, cardiorespiratory fitness and cardiovascular risk. Secondary measures collected at Weeks 8 and 26 will include self-efficacy, depression, perception of physical activity, participation, and health-related quality of life.

#### Primary

Physical activity will be measured over 4 days using a triaxial accelerometer (activPAL3™, PAL Technologies Ltd., Glasgow, UK) secured to the middle of the anterior non-paretic thigh and reported as steps/day. This device has been shown to demonstrate concurrent validity for step count, by demonstrating low error (1.6%) and high concurrence with direction observation (ICC 0.99, 95% CI 0.98 to 1.0) in people with stroke walking in an outdoor circuit [37], and test-retest reliability when walking indoors across days (ICC 0.98, 95% CI 0.93–0.99) [37].

#### Secondary

Walking ability will be measured using the 6-min Walk Test and the 10-m Walk Test. The 6-min Walk Test will be conducted according to the American Thoracic Society guidelines [38] and reported as distance walked in m. It is commonly used as a functional submaximal measure of oxygen uptake and exercise capacity [39] and is a valid and reliable clinical measure of walking ability in stroke survivors [40]. The 10-m Walk Test will be conducted at preferred and fast speeds over a 15 m course to remove any acceleration and deceleration, using usual gait aids, and reported as mean (SD) speed in m/s.Cardiorespiratory fitness will be measured from the 6-min Walk Test and reported as VO_2_Peak in ml/kg/min [41]. Heart rate, blood pressure, rate pressure product (systolic arterial pressure x heart rate) and VO_2_Peak will be recorded at rest and during the 6-min Walk Test, by a fully portable compact metabolic system using breath by breath analysis (Metamax 3B, Cortex, Biophysik, Germany) shown to be stable over time and accurate when tested against a gold standard criterion [42]. Test-retest reliability of cardiorespiratory variables measured using the Metamax 3B has been demonstrated for people with stroke when completing the 6-min Walk Test (ICCs range 0.76–0.97, error < 4%) [43].Cardiovascular risk will be measured from lipid profile and inflammatory markers. A finger stick will be taken and immediately analysed on a point of care device (Cholestech LDX, Alere™, Brisbane) [44] for lipid profile: total cholesterol (TC), low density lipoprotein (LDL), high density lipoprotein (HDL), ratio of total cholesterol to HDL (TC/HDL) and triglycerides (TRG). This instrument has been shown to have excellent validity compared to gold standard laboratory analysis [44]. Lipid profile measures for the Cholestech LDX had ICCs ranging from 0.87–0.99. A blood sample will be taken and analysed for inflammatory markers (high sensitivity CRP) [25].Self-efficacy of walking ability will be measured using the Ambulatory Self-Confidence Questionnaire, which has demonstrated reliability and validity in the older population [45]. The 22 items will be reported as a score from 0 to 10 where 0 is no confidence.Depression will be measured using the Hospital and Anxiety Depression Scale [46] and reported as a score from 0 to 21 on the depression subscale, where 0 is no depression. It has established validity in people with stroke [47].Perception of physical activity will be measured using the Physical Activity Scale for Individuals with Physical Disabilities in the domains of home repair, lawn and garden work, housework, vigorous sport and recreation, moderate sport and recreation, and occupation and transportation and the 13 items reported as a score from 0 to 100 MET hr./day, where 0 is no activity [48]. This survey has demonstrated criterion validity and test-retest reliability [49].Participation will be measured using the Impact on Participation and Autonomy Questionnaire [50] in the domains of indoor and outdoor autonomy, family role, social relations, work and education and the 31 items reported as a score from 30 to 155, where 30 is very little impact. It has demonstrated validity and test-retest reliability (ICC 0.83 to 0.91) in people with chronic disorders [51].Health-related quality of life will be measured using the EuroQual-5D [52] in the domains of mobility, usual activities, personal care, pain/discomfort and anxiety/depression as well as a measure of overall health state using a visual analogue scale. The domains will be reported as a utility score between 0 and 1, and the overall health state reported between 0 and 100, where 0 is poor health. It has established psychometric properties in people with stroke [53].

Data quality will be maintained by assessors being experienced physiotherapists trained in the collection of outcome measures. Double data entry will be performed separately by two research assistants blind to group allocation to reduce the potential for transcription error. All data will be de-identified to maintain confidentiality during and after the trial. Participants will receive a summary of results at the completion of the trial.

### Sample size

One hundred twenty eight participants will be recruited. The sample size has been calculated to be able to detect an effect size of 1200 steps/day with 80% power at a two-tailed significance level of 0.05. This between-group difference was based on an estimate that participants would take 4000 (SD 2000) steps/day at baseline and that the control intervention would increase this to 5200 step/day and the experimental intervention would increase this to 6400 steps/day, putting them above a sedentary level for older adults [54]. The smallest number of participants to detect a difference in physical activity of 1200 steps/day between two groups estimated from independent samples is 55 participants per group. On the assumption from previous trials with this population that approximately 15% of the participants may be lost to follow up during the course of the study, we have set a target of 128 participants in total. In order to reach the target sample size, the trial will be carried out across multiple centres, and a researcher will be employed to screen all stroke survivors at each centre.

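### The 55 per group does not follow from the printed inputs, which need 45; an input is unstated, or the 55 or the 80% power is misstated

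*Protocol article*

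**What the plan says.** All the figures are in the Sample size section of the protocol article.

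- **Target:** the trial is sized for an "effect size of 1200 steps/day with 80% power at a two-tailed significance level of 0.05".
- **Origin of the difference:** the starting assumption is "participants would take 4000 (SD 2000) steps/day at baseline". For follow-up, the section expects this: "the control intervention would increase this to 5200 step/day and the experimental intervention would increase this to 6400 steps/day". The gap of 6400 − 5200 = 1200 is consistent with the target.
- **Result, for each group:** "The smallest number of participants to detect a difference in physical activity of 1200 steps/day between two groups estimated from independent samples is 55 participants".
- **Allowance for loss, with both groups combined:** "approximately 15% of the participants may be lost to follow up during the course of the study, we have set a target of 128 participants".

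The SD of 2000 is the only measure of spread given, and it belongs to the baseline mean of 4000. The section gives no SD for Week 8, for Week 26 or for change from baseline. It mentions no adjustment of alpha for two time points and no allowance for centre or covariates.

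**The concern.** The section prints a difference, an SD, a power, an alpha and a type of comparison, and then calls 55 per group the smallest number that meets them. Those are all the inputs a two-sample calculation needs, so a reader should be able to recover the 55. The calculation gives 45 instead. The difference between a normal approximation and a t test is one participant per group, so neither that nor rounding explains a gap of ten.

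The figure concerns the primary outcome, steps/day, and each possible explanation describes a different design. If 2000 is the outcome SD, the power is not 80%. If a larger outcome SD was used, the SD that sized the trial has been left out. If alpha was reduced, the printed 0.05 is not the level that was used. At stake is whether the stated justification can be checked.

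**Working it through.** **Inputs, all from the Sample size section unless noted.** Difference 1200 steps/day; SD 2000 (stated for baseline, used here as the outcome SD because no other is given); two-sided alpha 0.05; power 80%; two independent samples. Equal allocation comes from the Randomisation section.

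**Step 1: attempt to reproduce 55.**

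Normal approximation: n per group = 2 × (SD/difference)² × (z for alpha + z for power)²
= 2 × (2000/1200)² × (1.96 + 0.8416)² = 43.6, so 44.

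Two-sample t test (noncentral t, standardised difference 1200/2000 = 0.6): 44.6, so 45.

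The 55 is not reproduced. It exceeds 45 by 10/45 = 22%.

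**Step 2: power on the printed inputs (t test).**

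| Per group | Power |
|---|---|
| 44 | 79.5% |
| 45 | 80.4% |
| 54 | 87.1% |
| 55 | 87.7% |

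The normal approximation gives 88.2% at 55. The row for 54 matters because 128 × 0.85 = 108.8, or about 54 per group after the assumed loss.

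**Step 3: conventional variants with SD 2000 and difference 1200.**

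| Variant | n per group (normal approximation to t test, rounded up) |
|---|---|
| One-sided 0.05, 80% power | 35 to 36 |
| Two-sided 0.05, 85% power | 50 to 51 |
| Two-sided 0.05, 90% power | 59 to 60 |
| Rank-test allowance on 45 (45/0.955 to 45/0.864) | 48 to 53 |

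None gives 55.

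**Step 4: single changes that do give 55.**

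- Outcome SD of about 2226 by t test, or 2246 by the normal approximation: roughly 2230.
- Two-sided alpha 0.025: 54.1 by t test, so 55 (53 by the normal approximation).
- Intended power of about 88%.
- A difference of about 1078 steps/day.
- A change-score analysis with SD 2000 at each time and a correlation of about 0.37 to 0.38, since 2000 × √(2 × (1 − 0.375)) = 2236.

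The section prints none of these.

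**Step 5: the step from 55 to 128.** 55 × 1.15 = 63.25, rounded up to 64 per group, gives exactly 128. By the stricter convention, 110/0.85 = 129.4. Keeping 110 of 128 allows a loss of 1 − 110/128 = 14.1%, which fits a loss described as approximate.

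**The case against.** The strongest reply is that nothing printed need be false. The SD of 2000 describes baseline, as part of the reasoning behind the difference, and the paragraph never calls it the outcome SD. Mean steps are expected to rise from 4000 to 5200 and 6400. A modestly larger spread at follow-up is plausible, though that is an assumption because the document is silent. With an outcome SD of about 2226, 55 per group is right at 80% power and two-sided 0.05. This stands. A reader might infer that the stated power, SD or alpha must be wrong, and the document does not support that. It supports only that the 55 cannot be recovered from what is printed.

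A second reply is that the discrepancy is on the safe side. This also stands on the printed inputs: the design delivers more than the 80% it promises, and 54 per group still gives 80% at an SD of 2200.

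Three other readings are tempting and should not be drawn:

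- **That the loss allowance is miscalculated.** Adding 15% and rounding up gives exactly 128, and even the stricter convention differs by only one or two participants in total.
- **That a null result could not be interpreted.** The Statistical analysis section commits to a mean difference with a 95% CI. The interval, not the design-stage power, shows which differences are excluded.
- **That the trial is underpowered because follow-up SDs will be much larger.** The document gives no such SDs, so any power computed from them is a scenario and not an error in the plan.

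The replies do not remove the mismatch itself. The paragraph presents 55 as a minimum, and with its only SD the minimum is 45.

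**Conclusion.** The point holds as a reporting and arithmetic defect of moderate severity. If SD 2000 applies to the outcome, the stated target needs 45 per group, the stated 55 is 22% higher, and its power is about 88% (about 87% with 54 completers per group). Either an input is unstated, such as an outcome SD of about 2230 or a two-sided alpha of 0.025, or the 55 or the 80% is misstated. The document does not allow a choice between these.

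The result assumes a plain two-sample comparison, as the section describes, with equal groups and a common SD. It does not show that the trial is too small, and it is no reason to reduce recruitment to 45 per group: if the larger SD was the real input, that cut would lose the intended power.

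**What to change.** Keep 128. The sponsor should first establish where the 55 came from, then amend the paragraph in one of these ways:

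- **If another input was used:** state it, whether the outcome SD (with the time point it refers to) or the adjusted alpha. The 55 and the 80% can then stand.
- **If 2000 was the outcome SD:** restate the result, for example that 128 randomised, leaving about 54 per group after 15% loss, gives about 87% power for 1200 steps/day at SD 2000 and two-sided 0.05. Remove the description of 55 as the smallest number.

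The second wording should not be adopted by default. If 55 rested on a larger SD, it would overstate the power. The loss allowance needs no change.

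The cost is a sentence or two of text. Recruitment, allocation, outcomes and analysis are unaffected.

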### Statistical analysis

Primary and secondary outcomes including physical activity, walking ability, cardiorespiratory fitness, cardiovascular risk, self-efficacy, perception of physical activity, participation, and quality of life will be reported as point estimates and measures of variability. An intention-to-treat between-group analysis will be performed on all outcome measures. Between-group differences will be analysed using generalized mixed effects models for continuous data, since this analysis does not require casewise deletion due to missing data. Data will be presented as mean difference (95% CI). Baseline characteristics judged to be clinically different between groups may be included as covariates.

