### Randomisation

Randomisation will be computer-generated, independent and concealed. The allocation sequence has been computer-generated by an independent researcher not involved in this study. For each centre, allocation to the experimental or control group will occur in random permuted blocks, so that after every block (of 4–6 participants), the experimental and control group will contain equal numbers [31]. Group allocation is stored in numbered, opaque envelopes in order to provide secure randomisation. After baseline measures have been collected, the therapist providing the intervention opens the envelope and reveals the group allocation. In this way, the allocation sequence is concealed from on-site recruiters.

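### Covariates may be picked, at discretion, from observed baseline differences, so the primary estimate is not fixed in advance and the use of Week 0 steps/day is left open

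*Protocol article*

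**What the plan says.** The Statistical analysis section of the protocol article names the model: "Between-group differences will be analysed using generalized mixed effects models for continuous data". It gives one rule for covariates: "Baseline characteristics judged to be clinically different between groups may be included as covariates". It lists no covariates, sets no threshold for a clinically relevant difference and does not say who judges. The verb makes inclusion optional even when a difference has been found.

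Under Measurement, "the primary outcome will be physical activity measured as steps/day over four days at Weeks 0, 8, 26", so a baseline value of the primary outcome is collected. No section says whether that value enters the model as a covariate, as one of the repeated responses, or not at all.

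The Sample size section treats the groups as independent samples and makes no allowance for baseline adjustment. Under Randomisation, permuted blocks are formed within each centre. Under Methods, data analysts are blind to allocation.

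**The concern.** With concealed randomisation, an observed baseline difference is a chance event. A covariate earns its place by predicting the outcome, not by happening to differ between groups. The stated rule uses the second criterion and adds two discretionary steps: whether a difference counts, and whether to adjust once it does. The primary estimate is therefore not uniquely defined until the baseline comparison has been seen.

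Two things are at stake. One is precision: a baseline measurement of the primary outcome may be used only sometimes, or not at all. The other is calibration: a test whose form depends on the baseline comparison need not hold the two-sided 0.05 level in the Sample size section, and the direction of the departure depends on how the discretion is exercised.

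**Working it through.** **Inputs from the article (Sample size, Randomisation).** Difference 1200 steps/day ("The sample size has been calculated to be able to detect an effect size of 1200 steps/day"); SD 2000 ("participants would take 4000 (SD 2000) steps/day at baseline", given for baseline, with no follow-up SD stated); "with 80% power at a two-tailed significance level of 0.05"; equal allocation; 128 recruited; 15% loss. Completers per group: 128 × 0.85 / 2 = 54.4.

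**Assumed, not in the article.** Follow-up SD also 2000; baseline to follow-up correlation r of 0.3, 0.5 or 0.7; an imbalance trigger of 0.25 SD, which is 500 steps/day.

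**The plan's own figure.** n per group = 2 × (1.960 + 0.842)² × 2000² / 1200² = 43.6, so 44 (45 with the t distribution). The article says "between two groups estimated from independent samples is 55 participants per group". The 55 does not reproduce, but that is a separate matter. Here it means only that the trial has more than its nominal 80% power on its own inputs.

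**Power with and without baseline adjustment, 54.4 per group.** Power = Φ(1200 / SE − 1.96), with SE = SD × √(2/54.4).

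- Follow-up values only: SD 2000, SE 383.
- Baseline as covariate: SD = 2000 × √(1 − r²).
- Unconstrained change from baseline: SD = 2000 × √(2(1 − r)).

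| r | Follow-up only | Baseline as covariate | Change contrast |
|---|---|---|---|
| 0.3 | 87.9% | 90.7% | 75.3% |
| 0.5 | 87.9% | 95.1% | 87.9% |
| 0.7 | 87.9% | 99.2% | 98.1% |

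The difference detectable with 80% power is (1.960 + 0.842) × SE: 1074 steps/day for follow-up values only, and 1025, 930 and 767 with baseline as covariate.

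**How often an imbalance rule would act.** At 55 per group the standard error of the baseline difference is 2000 × √(2/55) = 381 steps/day. A chance imbalance above 500 steps/day occurs with probability 2 × Φ(−500/381) ≈ 0.19, and one above 1000 with probability of about 0.01.

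**Simulation, 40,000 trials per setting, 55 per group, 0.25 SD trigger.**

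| r | SE never adjusted | SE always adjusted | SE if triggered | Power if triggered | Type I error if triggered | Type I error, smaller p-value of the two |
|---|---|---|---|---|---|---|
| 0.3 | 381 | 365 | 371 | 88.5% | 4.6% | 6.3% |
| 0.5 | 380 | 332 | 351 | 90.3% | 3.9% | 7.3% |
| 0.7 | 381 | 272 | 315 | 92.6% | 2.5% | 8.2% |

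Always adjusting and never adjusting both hold the 5% level. The triggered rule falls below it and recovers only part of the precision. The last column requires running both analyses and reporting the more favourable one.

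**The case against.** **Week 0 may already be used.** The rule speaks of baseline characteristics, a term the article does not define. Week 0 steps/day is listed as a measurement of the primary outcome, so it could enter every mixed model as a response. A reader might infer from the covariate rule that baseline steps/day is adjusted for only when the groups differ; the text does not say so. This stands, and it limits the precision argument. A longitudinal model with a common baseline mean would recover most of the gain. An unconstrained change contrast comes close at r = 0.7 (98.1% against 99.2%) but matches the unadjusted analysis at r = 0.5 and is worse at r = 0.3.

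**The role of Week 0 could be left to the analysis plan.** As a bare omission, yes. The covariate rule is not an omission: it is stated, and an analysis plan that followed it would inherit the problem.

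**Type I error inflation is not shown.** A reader might infer that the rule inflates false positives to 7% or 8%. Applied mechanically with the assumed trigger, it does the reverse. The inflated figures are an upper bound for choosing between two analyses, and the article describes no such conduct.

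**Analysts are blind.** This hinders steering the result towards one arm. It does not hide a difference between two unlabelled groups, and it does not stop a choice made for significance.

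**Power is adequate anyway.** Agreed: about 88% on the article's own inputs without any adjustment.

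**Conclusion.** The point holds as a fault in a stated rule. Covariates may be chosen, optionally and by judgement, from differences seen between randomised groups, so the primary estimate is not settled before the data are seen. The article does not commit to using Week 0 steps/day and does not state its role in the model.

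The size is conditional. Against a follow-up-only comparison, always adjusting takes power from about 88% to about 91% to 99%, assuming r of 0.3 to 0.7 and SD 2000 at follow-up. If the model already uses Week 0, the gain depends on how: little with a common baseline mean, about one percentage point over a change contrast at r = 0.7, and more at lower r. The stated rule does not by itself inflate type I error in the case examined.

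None of this makes the trial invalid or underpowered on its own inputs. The sentence should be changed because doing so fixes the primary estimate in advance and secures precision from data already being collected.

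**What to change.** Replace the covariate sentence in the Statistical analysis section with:

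> The primary model will include Week 0 steps/day as a covariate, or constrain baseline means to be equal in the longitudinal model, and will include centre, by which randomisation is blocked. Each other outcome measured at Week 0 will be adjusted for its own baseline value. Any adjustment for characteristics selected on observed between-group differences will be a labelled sensitivity analysis.

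The own-baseline clause applies to walking ability, cardiorespiratory fitness and cardiovascular risk. The questionnaire outcomes are listed for Weeks 8 and 26 only. The change rewrites one short passage, needs no extra data, visits or participants, and should be made before any between-group baseline comparison is seen.

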## Discussion

This study has the potential to reduce disability and burden of care in people with a major health condition that has a high personal and community cost. Heart, stroke and vascular diseases are collectively one of the leading causes of premature death and disability in the developed world. More than 75% of people with stroke have coronary heart disease and are 2–3 times more likely to be hospitalised with coronary heart disease and heart failure than the rest of the population [55], which contributes to high health costs. Low levels of physical activity are a known risk factor of coronary heart disease. After stroke, people have low levels of physical activity. This research will provide evidence of the effect of the application of a commercially available technology (treadmill training), used in a manner (high-intensity) that will enable stroke survivors to increase their fitness, thereby improving physical activity in the short-term. It is also anticipated that the self-management aspect of the intervention will result in the maintenance of high physical activity in the long-term, thereby improving quality of life and reducing the burden on others. Given the major demographic shift in developed nations involving significant growth in the aged population, this research could make an important evidence-based contribution to the promotion of healthy ageing.
